### Experimental procedures

Eligible participants will receive a detailed explanation of the test methods and procedures. Upon obtaining their informed consent and basic personal data, they will undergo a normal-speed 10-meter walk test and surface electromyographic measurement of lower limb muscles in an EMG room maintained at 25°C.

### Muscles to be tested

Based on the relevant literature and preliminary data analysis, the muscles selected for testing in this study are the rectus femoris, semitendinosus, tibialis anterior, and the medial head of the gastrocnemius in both lower limbs of older adult participants.

### Test program

(1)Instrument preparation and electrode placement: Surface EMG signals will be collected using the Dinuo Surface EMG Analyzer and Feedback Instrument (Zhejiang Dinuo Medical Science and Technology Co., Ltd., model SG-800A). Before testing, the instrument is adjusted and set to a sampling frequency of 2000 Hz. This wireless EMG testing method, in contrast to wired electrodes, offers greater convenience and less interference with actions, suitable for a broader range of application scenarios. Participants will be required to expose the skin of their lower limbs, depilate any excessive hair on the muscle surface, and disinfect and degrease the designated testing area using a 75% alcohol cotton ball. Electrodes are placed once the skin has dried to minimize impedance. Placement of all recording electrodes adheres to the European recommendations of the Surface ElectroMyoGraphy for the Non-Invasive Assessment of Muscles (SENIAM). Single-use EMG recording electrode patches (Zhejiang Dinuo Medical Technology Co., Ltd., model E5) are affixed to the rectus femoris (midpoint between the anterior superior iliac spine and the patella’s upper edge), semitendinosus (midpoint between the ischial tuberosity and the tibia’s medial epicondyle), tibialis anterior (one-third along the line from the fibula’s tip to the inner ankle’s tip), and medial head of the gastrocnemius (muscle’s most prominent bulge). Electrodes are placed on the muscle belly’s most prominent part, parallel to the muscle fibers. A reference electrode patch is placed on a non-tested muscle to avoid test interference. Electrodes are secured with elastic bandages to prevent displacement and movement during the walk, thereby reducing motion artifacts. The illustration of electrode placement and bandage fixation is shown in Fig 2.

**Fig 2 pone.0325356.g002:**
[figure not shown]
Figure of electrode placement and bandage fixation for surface electromyography recording.

(2)10-meter walk test: A 12-meter stretch will be marked on an open and flat 15-meter walkway, incorporating a 10-meter timed section flanked by 1-meter zones for acceleration and deceleration at both ends. After the surface EMG recording and reference electrodes have been properly placed, subjects will be instructed to stand still and relaxed at the starting line, with the aim of maintaining the EMG signal near the baseline (<10 μV) as displayed on the instrument. Upon the ‘start’ signal, participants will walk to the finish line at a comfortable pace, maintaining a natural walking speed. The time taken to traverse the 10-meter timed section will be recorded using a timer, and dynamic sEMG parameters of the lower limb muscles will be captured by the surface EMG device, complemented by recordings of different gait cycles using an infrared camera system for further analysis. Typically, three tests will be conducted with 1–2 minutes of rest between each, and the average result of these three tests will be calculated. The entire test will require the accompaniment of a researcher to ensure safety, without any physical contact, and no assistive devices will be used by the subjects during the test.

### Data processing

Surface EMG data analysis will be performed using the proprietary wireless surface EMG analysis feedback software (Zhejiang Dino Medical Technology Co., Ltd.). Data from five gait cycles following the third cycle (i.e., the 4th to 8th gait cycles) will be analyzed. First, the surface EMG signals will be band-pass filtered using a zero-delay Butterworth filter between 20 and 500 Hz to remove noise and irrelevant frequencies from the signals. Afterward, adaptive filtering will be applied to eliminate ECG interference. Once filtering is complete, an analyst will visually inspect the raw EMG data to identify any motion artifacts or noise. The EMG signals will then be rectified and smoothed (using averaging) to convert negative values into positive ones and ensure signal smoothing. However, smoothing filters will not be applied for frequency-domain analysis. To reduce inter-individual variability, the maximum value of the rectified EMG signals (EMG_max) will serve as a benchmark for normalization. Finally, the rectified EMG signals from the 5 gait cycles will be normalized to EMG_max, meaning that all EMG values will be expressed as a ratio relative to EMG_max.

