## Introduction

As global aging dynamics intensify, frailty has emerged as a major challenge to healthy aging. Frailty is a clinical syndrome of increased vulnerability and dysfunction due to the cumulative decline of multiple body systems, characterized by unconscious weight loss, reduced grip strength, slowed gait, decreased physical activity and self-reported fatigue, which significantly increases the risk of adverse health outcomes such as falls, disability and death [1–3], and imposes a serious economic burden on the families of patients, making social security for old-age and health care more challenging [1,4,5]. However, the process of frailty can be delayed and reversed, and effective interventions can prevent the occurrence of adverse events in older adults in the pre-frailty stage and delay the entry into the frailty stage, or even recover from the pre-frailty stage to a non-frailty state [1,6], so early screening and identification of high-risk groups is an important part of the optimal management of frailty in older adults.

Slowed gait speed is a component of the frailty phenotype, and studies have shown significant decreases in gait speed in frail older adults, whether they are walking at habitual speeds or walking at fast speeds [7–9]. While gait speed can predict frailty and some adverse health outcomes [10–12], numerous factors in daily life can slow walking speed in older adults, making it a less effective predictor when considered in isolation. Decrements in walking ability may be related to reductions in muscle mass, muscle contractility, balance, and other physiological factors [13–15], with decreased strength and endurance in lower limb muscles strongly correlated with heightened frailty risk [16]. Notably, the rectus femoris, semitendinosus, tibialis anterior, and medial head of gastrocnemius are critical to walking; reductions in their strength may be pivotal to the observed deceleration in gait speed [17,18]. These observations suggest that changes in the biomechanical parameters of lower limb muscles could underpin the pathophysiology of frailty, and identifying these characteristic changes is crucial for developing effective frailty screening, prevention, and rehabilitation programs.

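### The sEMG window is fixed by cycle count (cycles 4 to 8) and not tied to the 10 m timed section, so for longer strides its end may fall in the deceleration zone

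*Protocol article*

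**What the plan says.** Under Test program, item (2), the course is laid out by distance: "A 12-meter stretch will be marked on an open and flat 15-meter walkway". The plan divides this stretch into three parts, described as "incorporating a 10-meter timed section flanked by 1-meter zones for acceleration and deceleration at both ends". At the start, "subjects will be instructed to stand still and relaxed at the starting line"; then "participants will walk to the finish line at a comfortable pace, maintaining a natural walking speed". There are three walks, and "the average result of these three tests will be calculated". Gait cycles are also recorded with an infrared camera system.

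Under Data processing, the analysed signal is chosen by count: "Data from five gait cycles following the third cycle (i.e., the 4th to 8th gait cycles) will be analyzed". The article does not say whether cycle 1 begins at the starting line or at the start of the timed section. It does not require the chosen cycles to lie in the timed section, and it does not say what happens if a walk yields fewer than eight usable cycles.

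The objectives require four muscles in both legs. The time-domain and frequency-domain parameters, with the symmetry index and contribution rates derived from them, are primary outcomes.

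**The concern.** Skipping three cycles removes the start from standstill. Nothing equivalent protects the other end, although the protocol itself marks a zone there for slowing down. With a window set by count and a course set by distance, the place where the window ends depends on stride length: short strides finish cycle 8 well before the end, and long strides finish it close to the end or beyond.

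This matters because of the comparison being made. If stride length differs between frail and non-frail participants, the two groups are sampled at different places in the walk, and part of any sEMG difference could reflect place and not frailty. Three features of the plan bear on this:

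- Averaging three walks does not remove an effect that recurs in each of them.
- Amplitudes are divided by the maximum rectified value. If that maximum fell in a slowing cycle, it would rescale all five cycles.
- The symmetry index compares left with right RMS. The two legs' windows end half a stride apart, so one leg's window could include slowing when the other's does not.

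**Working it through.** **Inputs from the article.** The layout reproduces: 1 + 10 + 1 = 12 m, so the timed section runs from 1 m to 11 m and the deceleration zone from 11 m to 12 m. Cycles 4 to 8 are five cycles, with three skipped, so eight are needed.

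**Assumptions.**
- Stride length L is constant and between 0.8 and 1.5 m (the article gives none).
- The starting line is at 0 m and the finish line at 12 m.
- The other leg's cycles lag the leading leg's by half a stride.

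**Formula.** With counting origin x0 (0 m for the starting line, 1 m for the start of the timed section), the leading leg's window runs from x0 + 3L to x0 + 8L, and the other leg's from x0 + 3.5L to x0 + 8.5L.

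**Largest stride that keeps cycle 8 before the deceleration zone (11 m) or on the marked stretch (12 m).**

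| Counted from | Leg | Ends by 11 m | Ends by 12 m |
|---|---|---|---|
| Starting line | leading | 11/8 = 1.375 m | 12/8 = 1.50 m |
| Starting line | other | 11/8.5 = 1.29 m | 12/8.5 = 1.41 m |
| 1 m line | leading | 10/8 = 1.25 m | 11/8 = 1.375 m |
| 1 m line | other | 10/8.5 = 1.18 m | 11/8.5 = 1.29 m |

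**End of cycle 8 (m) over the assumed range.**

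| L (m) | Starting line, leading (8L) | Starting line, other (8.5L) | 1 m line, leading (1 + 8L) | 1 m line, other (1 + 8.5L) |
|---|---|---|---|---|
| 0.8 | 6.4 | 6.8 | 7.4 | 7.8 |
| 1.0 | 8.0 | 8.5 | 9.0 | 9.5 |
| 1.2 | 9.6 | 10.2 | 10.6 | 11.2 |
| 1.3 | 10.4 | 11.05 | 11.4 | 12.05 |
| 1.4 | 11.2 | 11.9 | 12.2 | 12.9 |
| 1.5 | 12.0 | 12.75 | 13.0 | 13.75 |

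**Share of the window past 11 m, counted from the starting line.** The window is 5L long.
- L = 1.4 m, leading leg: 0.2/7.0 = 3%.
- L = 1.4 m, other leg: 0.9/7.0 = 13%, which is 0.9/1.4 = 64% of cycle 8.
- L = 1.5 m, leading leg: 1.0/7.5 = 13%.
- L = 1.5 m, other leg: 1.75/7.5 = 23%, which is all of cycle 8 and a little of cycle 7.

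**Sensitivity (leading leg, from the starting line).** If the first cycle from standstill covers only 0.75L, the 11 m limit rises to 11/7.75 = 1.42 m. If slowing begins 2 m before the 12 m mark, it falls to 10/8 = 1.25 m.

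**Would a window inside the timed section always be available?** Five cycles of one leg need six contacts of that foot. A 10 m section always contains six if 10/L is at least 6, so five whole cycles per leg are guaranteed for L up to 10/6 = 1.67 m, wherever the feet fall. For both legs together the least length needed is 5.5L, so 10/5.5 = 1.82 m is the limit with favourable placement.

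**The case against.** The strongest reply is that the rule works for much of the plausible range. Starting from standstill at the starting line makes that line the natural origin for counting, and skipping three cycles then reads as discarding gait initiation. On that reading eight cycles fit the 12 m for strides up to 1.50 m (1.41 m for the other leg) and stay in the timed section up to 1.375 m (1.29 m). At 1.3 m the other leg overruns by 5 cm. Participants are told to keep a natural speed to a finish line whose position is not stated, and the 15 m walkway leaves 3 m beyond the marked 12 m. All of this stands, and it limits the size of the problem. It does not supply the missing guard at the end of the walk.

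A reader might infer more: that the window does not fit the course for normal strides, that controls are in fact sampled while slowing, or that they will lack an eighth cycle. The documents do not support this. They give no stride length or cadence for either group. The Introduction reports that "studies have shown significant decreases in gait speed in frail older adults", and slower walking need not mean shorter strides. Nothing in the article quantifies how slowing changes any of the sEMG parameters. Missing eighth cycles would require long strides together with no usable walking beyond the finish line, and neither is documented.

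Segmentation detail could also sit in the full protocol or in operating procedures. That excuses silence on the counting origin. It does not answer the rule that is stated, which is by count alone.

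**Conclusion.** The point holds as a weakness in how the window is defined. At strides above 1.375 m (leading leg) or about 1.29 m (other leg) counted from the starting line, or above 1.25 m and about 1.18 m counted from the 1 m line, the end of the window may be recorded in the protocol's own deceleration zone. Below those values the window lies in mid-walk.

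For strides of 1.4 to 1.5 m counted from the starting line, the overlap is 3% to 13% of the window for the leading leg and 13% to 23% for the other, mostly in cycle 8. The bias would be differential only if stride length differs by group, which is plausible but not stated. Its effect on the sEMG parameters is unknown and probably modest.

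The conclusion rests on constant stride length, a half-stride lag between legs and a finish line at 12 m. Confidence is moderate. The change is worth making because it is cheap and concerns the primary outcomes.

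**What to change.** In Data processing, replace the count-based window with a rule by position, for example: *five consecutive gait cycles lying wholly within the 10 m timed section, nearest its midpoint, taken separately for each leg in every participant and identified from the gait-cycle recordings.* This also settles the counting origin. Add one clause on what is done if a walk does not yield five such cycles, which can happen only for strides above about 1.67 m. Re-cut recordings already made by the same rule, so that all participants are treated alike.

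The cost is about one sentence and the re-segmentation of stored recordings. No repeat walks are needed if the infrared camera covers the timed section; the article does not say that it does, and otherwise the cycles should be segmented from another recorded gait event. A small downside is that the cycle numbers analysed will differ between participants.

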### Ethics and dissemination

The study will be conducted according to the guidelines of the Declaration of Helsinki and has been approved by the Ethics Committee of Xiamen Cardiovascular Hospital of Xiamen University (Ethical Approval No. [2023] Medical Ethics Science No. 39; approval date: November 8, 2023). Before participation, research assistants will provide a comprehensive explanation of the study’s objectives, methods, potential risks, and benefits, followed by obtaining written informed consent from each participant. Participants will have the right to withdraw at any time without affecting their medical care. All relevant data from the research process will be accurately recorded in the Case Report Forms designed by the research team for subsequent organization and analysis (S2 Appendix).

Access to participant data will be limited to authorized team members only, and all personal identifiers will be removed. Participants will be assigned unique identifiers to ensure confidentiality. The collected data will be securely stored and used exclusively for the purposes defined in the study protocol.

The dissemination of the results will be conducted irrespective of the outcome. Findings will be submitted for publication in peer-reviewed journals and presented at relevant scientific conferences. Summaries of the results will also be made available to participants upon request. All publications and presentations will be based on data that has been fully anonymized to protect participant privacy.

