### Participants

Recruitment for the study will take place from November 2024 to April 2025 using non-randomized convenience sampling. Seventy-five older adults from the inpatient and outpatient departments of the Xiamen Cardiovascular Hospital of Xiamen University in China, who are assessed as frail using the Fried’s frailty phenotype [24], will be selected for the case group. An additional 75 non-frail older adults, matched by age, gender, and cultural background during the same period, will form the control group. All participants will sign an informed consent form (S3 Appendix) and undergo baseline assessments, which include comprehensive socio-demographic and clinical data collection, along with screening using the Fried’s frailty phenotype (S4 Appendix). A panel investigator will review the inclusion and exclusion criteria and assign participants to either the case or control group based on the Fried’s frailty phenotype screening results.

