### Outcome measures and calculation algorithms

#### Primary outcome.

The primary outcomes will include three time-domain indicators and two frequency-domain indicators calculated through software analysis, along with the symmetry index (SI), muscle activation sequences, and muscle contribution ratios derived from these indicators.

(1)The time-domain indicators will include root mean square amplitude (RMS), integral electromyography (IEMG), and average electromyography (AEMG), which are primarily related to muscle contraction force. The formulas for these calculations are as follows:

$$\begin{array}{c} RMS\;=\;\sqrt{\frac{\sum {\mathrm{\backslash nolimits}}_{i=0}^{N}Data{\left[i\right]}^{2}}{N}} \end{array}$$

$$\begin{array}{c} IEMG\;=\;\sum_{i=0}^{N}\left|Data[i]\right|\times \Delta t \end{array}$$

$$AEMG=\frac{1}{N}\sum_{i=1}^{N}\left|xi\right|$$

In the aforementioned formulas, Data[i]denotes the EMG signal value at the i-th sampling point. Nrefers to the total number of sampling points, which represents the number of data points collected over a specific time period. iis the index indicating the position of the data point, ranging from the first to the N-th. Δtrepresents the time interval between consecutive sampling points. xi denotes the absolute value of the EMG signal at the i-th sampling point.

(2)The frequency-domain indicators will include mean power frequency (MPF) and median frequency (MF), commonly used to assess muscle fatigue.

$$MPF=\frac{\sum {\mathrm{\backslash nolimits}}_{i=1}^{N}f_{i}\cdot P_{i}}{\sum {\mathrm{\backslash nolimits}}_{i=1}^{N}P_{i}}$$

MF=Median(f(P(f)))

In the aforementioned formulas, $f_{i}$represents the i-th frequency point, while $P_{i}$corresponds to the power spectral density value at the i-th frequency point. Nis the total number of frequency points. P(f)is the power spectral density as a function of frequency f, and frefers to the frequency point.

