### Quality control

In the present study, comprehensive quality control measures will be implemented to ensure that every stage from participant recruitment to data analysis is performed in strict accordance with standard operating procedures. All potential subjects will undergo a detailed screening process and sign an informed consent form prior to participation. Data collection will be carried out by professionally trained and accredited rehabilitation physicians and research assistants to ensure the accuracy and consistency of the questionnaires and related tests. To prevent data entry errors, a dual data entry system will be employed, and data will be regularly checked for completeness and accuracy. Data hypothesis testing will be conducted prior to statistical analysis to ensure that appropriate statistical methods are used and potential confounding variables are considered in the analysis. The study will adhere to strict ethical guidelines to safeguard participant privacy and data security, and participants will be allowed to withdraw from the study at any time. The entire process will be overseen by an independent quality control team to ensure high standards and reliability of the study. These measures will collectively ensure the validity of the study results and provide a solid scientific basis for understanding the characteristics of EMG signals in frail older adults.

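### No masking to case/control status is planned for the analyst who judges EMG artefacts by eye before the primary parameters are derived

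*Protocol article*

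**What the plan says.** Under Participants, a panel investigator is to "assign participants to either the case or control group based on the Fried’s frailty phenotype screening results". This happens at baseline, before the walk test and the recording.

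Under Data processing, the chain runs in order: gait cycles 4 to 8 are selected, the signal is band-pass filtered at 20 to 500 Hz, adaptive filtering removes ECG interference, and then "an analyst will visually inspect the raw EMG data to identify any motion artifacts or noise". Rectification, smoothing and normalisation follow. For normalisation, "the maximum value of the rectified EMG signals (EMG_max) will serve as a benchmark for normalization". Smoothing is omitted for the frequency-domain indices.

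Under Primary outcome, "The primary outcomes will include three time-domain indicators and two frequency-domain indicators calculated through software analysis"; the symmetry index, activation sequence and contribution rates are derived in addition.

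Two further places bear on who might know group. Ethics and dissemination states: "Participants will be assigned unique identifiers to ensure confidentiality". Quality control states: "Data collection will be carried out by professionally trained and accredited rehabilitation physicians and research assistants". That section also lists dual data entry and an independent quality control team. Masking of the analyst to group is not mentioned in either place or anywhere else in the article.

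**The concern.** Visual inspection is the one step in the signal chain that the article describes as a human judgement. The article states no criterion for calling something an artefact and does not say what happens to a flagged segment. In a case-control comparison, such a step is a recognised route for differential measurement error: a reader who knows who is frail may treat doubtful signal differently in the two groups.

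The article also gives a reader something to expect. Its Introduction suggests that reduced strength in these four muscles may lie behind slower gait. If ambiguous signal were read in line with that idea, part of a group difference could come from the reading rather than from the muscle. A larger sample would not remove such an error, and the logistic regression and ROC analyses would inherit it, because they use the same parameters.

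**Working it through.** The plan gives no figure for this point, so the check traces which outcomes the judgement can reach and by which route.

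**1. Order of events.** Group is assigned at screening (Participants). The signal is recorded afterwards (Experimental procedures), then inspected, then reduced to parameters (Data processing; Outcome measures). Group status therefore exists before the judgement is made. The article does not say whether the analyst has access to it.

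**2. Routes to each primary outcome, if flagged segments are dropped or altered.** Two routes need to be kept apart: (a) which samples remain, and (b) a change in EMG_max.

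- *RMS, IEMG, AEMG.* Both routes apply. These are sums or means over the retained samples, and the samples are divided by EMG_max. If removing one spike lowers EMG_max from M to M/k, every other normalised value is multiplied by k.
- *MPF.* Only route (a) applies. Dividing the signal by a constant c divides each P_i by c². In MPF = Σ f_i·P_i / Σ P_i, the factor 1/c² cancels.
- *MF.* Only route (a) applies, because the frequency that splits the power in half is unchanged by rescaling.
- *SI = (left RMS − right RMS)/(left RMS + right RMS)* and *contribution rate* (one muscle's IEMG over the total). Route (a) applies. Route (b) applies if EMG_max is taken separately for each muscle, which the article does not state. A common factor would cancel.
- *Activation order.* Onset is the first time that a 10-sample mean exceeds 1.7 times the maximum of the first 20 samples. At 2000 Hz those 20 samples last 20/2000 s = 10 ms. A spike kept or removed there moves the threshold, so route (a) applies. Rescaling a channel by a constant moves signal and threshold together, so route (b) does not.

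All the primary parameters therefore lie downstream of the inspection, but the EMG_max route reaches only some of them.

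**3. Safeguards that are stated.** Identifiers: described for confidentiality only. Quality control: training, double entry and independent oversight. None of these is said to withhold group from the analyst.

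**4. Scale, by assumption only.** The article gives no bias figure. Suppose there is no true difference and the judgement shifts the two group means apart by b standard deviations. The rejection rate of a two-sided 5% t-test then follows from a noncentral t distribution with df = 2n − 2 and noncentrality b·√(n/2). For n = 67 and b = 0.20, the noncentrality is 0.20 × √33.5 = 1.16. The two sample sizes come from the Sample size calculation section.

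| Assumed b (SD) | n = 67 per group | n = 75 per group |
|---|---|---|
| 0.05 | 6.0% | 6.1% |
| 0.10 | 8.9% | 9.3% |
| 0.20 | 21.0% | 22.9% |
| 0.30 | 40.7% | 44.7% |

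For comparison, 0.20/0.433 = 0.46, so a shift of 0.20 SD would be just under half of the design effect size. The values of b are arbitrary, and the same table would hold for any bias in any two-group study of this size.

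**The case against.** The strongest reply is that this argues from silence. The article condenses a fuller protocol, refers to standard operating procedures and has appendices that are not shown. Group assignment, data collection and inspection are given to differently described people (a panel investigator, physicians and assistants, an analyst), and personal identifiers are removed. The text says that artefacts are identified, not that anything is deleted. Discretion is also limited: the cycles are fixed in advance, automated filtering comes first, software computes the indices, and three walks are averaged.

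Much of this stands, and it rules out several stronger readings that a reader might infer. The article does not show that the analyst is unmasked, that the codes reveal group, or that spikes are removed selectively. Nor does EMG_max rescaling distort every primary outcome, since MPF and MF are immune to it. The error rates tabulated above are not evidence about this study.

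What the reply does not remove is the point about conduct. The article sets out its signal processing and quality control in some detail, and masking the reader is not among the measures. Removing names is not the same as hiding group, and masking would not follow automatically from the plan as written. Who may know case status while the primary outcome is being derived is best settled before processing, not left to the statistical analysis.

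**Conclusion.** The concern holds in a limited form. A subjective artefact judgement precedes all the primary sEMG parameters, group is fixed beforehand, and no masking of the analyst is planned in the article. If flagged segments are dropped or altered and the analyst knows the group, bias is possible in the amplitude measures, the symmetry index, contribution rates and onset order. In MPF and MF it is possible through segment selection alone.

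Those two conditions are assumptions; the article confirms neither. The size and direction of any bias are unknown and cannot be derived from the article. It would be wrong to infer that the group comparison is already compromised. The supported conclusion is that an inexpensive protection against differential misjudgement is available and should be written in.

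**What to change.** Amend Data processing along these lines:

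- Artefact inspection and all EMG processing are done on files labelled with a group-neutral code, with neither Fried status nor group visible in the file name, list or header.
- The work is done by existing staff who took no part in that participant's screening or walk test.
- Artefact decisions, and what was done with each flagged segment, are recorded and locked before codes are linked to group.
- The number of rejected cycles is reported by group.

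The cost is relabelling the files and a short procedural addition; no extra reader or test is needed. Someone other than the analyst must hold the link file. Masking will be partial, because slow gait may be visible in the trace, and the report should say so. Study status and timeline places data analysis after the end of data collection, so the change can be made if inspection has not yet begun. If it has begun, the report should state what the analyst knew.
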